## Abstract

**Introduction:** The On&Out study is aimed at assessing the effectiveness, cost-utility and physiological underpinnings of the FIBROWALK multicomponent intervention conducted in two different settings: online (FIBRO-On) or outdoors (FIBRO-Out). Both interventions have proved to be efficacious in the short-term but there is no study assessing their comparative effectiveness nor their long-term effects. For the first time, this study will also evaluate the cost-utility (6-month time-horizon) and the effects on immune-inflammatory biomarkers and Brain-Derived Neurotrophic Factor (BDNF) levels of both interventions. The objectives of this 6-month, randomized, controlled trial (RCT) are 1) to examine the effectiveness and cost-utility of adding FIBRO-On or FIBRO-Out to Treatment-As-Usual (TAU) for individuals with fibromyalgia (FM); 2) to identify pre–post differences in blood biomarker levels in the three study arms and 3) to analyze the role of process variables as mediators of 6-month follow-up clinical outcomes.

**Methods and analysis:** Participants will be 225 individuals with FM recruited at Vall d’Hebron University Hospital (Barcelona, Spain), randomly allocated to one of the three study arms: TAU vs. TAU + FIBRO-On vs. TAU + FIBRO-Out. A comprehensive assessment to collect functional impairment, pain, fatigue, depressive and anxiety symptoms, perceived stress, central sensitization, physical function, sleep quality, perceived cognitive dysfunction, kinesiophobia, pain catastrophizing, psychological inflexibility in pain and pain knowledge will be conducted pre-intervention, at 6 weeks, post-intervention (12 weeks), and at 6-month follow-up. Changes in immune-inflammatory biomarkers [i.e., IL-6, CXCL8, IL-17A, IL-4, IL-10, and high-sensitivity C-reactive protein (hs-CRP)] and Brain-Derived Neurotrophic Factor will be evaluated in 40 participants in each treatment arm (total n = 120) at pre- and post-treatment. Quality of life and direct and indirect costs will be evaluated at baseline and at 6-month follow-up. Linear mixed-effects regression models using restricted maximum likelihood, mediational models and a full economic evaluation applying bootstrapping techniques, acceptability curves and sensitivity analyses will be computed.

**Ethics and dissemination:** This study has been approved by the Ethics Committee of the Vall d’Hebron Institute of Research. The results will be actively disseminated through peer-reviewed journals, conference presentations, social media and various community engagement activities. Trial registration number NCT05377567 (clinicaltrials.gov).

## 1 Introduction

Fibromyalgia (FM) is a highly prevalent syndrome (2.7% worldwide, 2.5% in Europe and 2.4% in Spain) (Queiroz, 2013) which mainly affects women, around 40–50 years of age (Häuser et al., 2015). FM is characterized by the presence of chronic widespread musculoskeletal pain, fatigue and sleep problems (Häuser et al., 2015) and, very often, it is also accompanied by anxiety (13%–63.8%) and depressive disorders (20%–80%) (Fietta et al., 2007). Remarkably, FM is the chronic pain condition with the highest rate of unemployment, sick leave, disability claims and absenteeism (Leadley et al., 2012) and 23%–66% of individuals with this syndrome are forced to leave work due to its aftermaths (Assefi et al., 2003; Gerdle et al., 2008). Furthermore, individuals with FM are usually considered “hyper-frequent users'' of health services with 6% of adult patients attending primary care and 10%–20% attending rheumatology services having a diagnosis of FM (Gerdle et al., 2008; Häuser et al., 2015). Regarding this latter point, FM is the medical condition presenting higher costs, with direct costs (i.e., medication, visits to healthcare professionals, medical tests, emergency room visits and hospital admissions) being up to three times higher than the observed in other chronic pain conditions and similar sociodemographic characteristics (Berger et al., 2007; Leadley et al., 2012; Wylezinski et al., 2019).

### 1.1 Recommended treatments for FM and the emergence of online and outdoors therapeutic approaches

Up to date, the available treatments for FM are not curative and their clinical efficacy is generally rather low (Häuser et al., 2015). In relation to pharmacological treatments, the European League Against Rheumatism (EULAR) recommends reserving pharmacological treatment only for those cases with severe pain and for sleep disturbances (Häuser et al., 2015; Macfarlane et al., 2017). In line with this, non-pharmacological strategies appear to promote broader clinical effects and show slightly larger effect sizes compared to pharmacological treatments (Nüesch et al., 2013, Perrot et al., 2014). Non-pharmacological strategies include interventions such as pain education, cognitive behavioral therapy (CBT), mindfulness, therapeutic physical exercise, among others, which aim primarily at alleviating symptoms and improving patients’ quality of life (Macfarlane et al., 2017). More specifically, Pain Neuroscience Education (PNE) (Van Oosterwijck et al., 2013; Nijs et al., 2014; Amer-Cuenca et al., 2020) is aimed at changing patients’ pain beliefs, emphasizing how overprotective behaviors can accentuate pain experience (Moseley and Butler, 2015). PNE has been found to be effective for reducing pain disability, catastrophizing, avoidance behaviors and physical inactivity in patients with FM (Malfliet et al., 2017). Concurrently, there is high agreement among clinical guidelines that CBT and therapeutic physical exercise should constitute the main therapeutic elements when treating FM (Jones et al., 2006; Bernardy et al., 2010; Sosa-Reina et al., 2017; Bernardy et al., 2018); furthermore, combining both interventions has been shown to be particularly effective (Witek-Janusek et al., 2008; Black et al., 2013). There is also mounting evidence that mindfulness training can be an efficacious and cost-effective approach for improving quality of life, functional impairment, anxiety, depression, and other symptoms in patients with FM (Haugmark et al., 2019; Pérez-Aranda et al., 2019).

Mounting empirical evidence suggests that multicomponent approaches integrating at least therapeutic physical exercise and a psychological/educational intervention can be effective in individuals with FM (e.g., Van Wilgen et al., 2007; Castel et al., 2013; Thieme et al., 2017) and some authors propose that these multicomponent interventions should be the “gold standard” in FM (Rivera et al., 2006; Häuser et al., 2008; De Miquel et al., 2010; Macfarlane et al., 2017; Thieme et al., 2017). In this regard, a metanalysis exploring the efficacy of different pharmacological and non-pharmacological therapies on fibromyalgia symptoms (Papadopoulou et al., 2016) suggested that multidisciplinary treatments would be the most beneficial ones among non-pharmacological interventions for treating FM, since statistically significant improvements were found in all FM symptoms comprising OMERACT-10 response criteria (i.e., pain, sleep, function, fatigue, anxiety, depression, cognition). Furthermore, four recent RCTs published after the aforementioned metanalysis, provided additional evidence on the short-term efficacy (i.e., post-intervention) of a 3-month multicomponent intervention for FM (i.e., the FIBROWALK program) comprising CBT, mindfulness training, therapeutic physical exercise and PNE (Serrat et al., 2020; Serrat et al., 2021a; Serrat et al., 2021b; Serrat et al., 2022b). Interestingly, the FIBROWALK program showed to be clinically efficacious when tested in hospital, outdoors and also in online settings compared to Treatment-As-Usual (TAU) alone and provided clinically relevant improvements in functionality, pain, kinesiophobia, physical function, fatigue, and anxiety and depressive symptomatology (Serrat et al., 2020; Serrat et al., 2021a; Serrat et al., 2021b; Serrat et al., 2022b).

The COVID-19 pandemic has enforced the emergence of new therapeutic approaches alternative to face-to-face treatment since mobility restrictions and infection risk have generally limited this classical format of therapy. In this regard, there is a growing body of evidence on the efficacy of alternative forms of therapy such as online (Schwamm et al., 2020; Weiling et al., 2020; Serrat et al., 2021a; White et al., 2022) and outdoor (Buckley et al., 2018; Stanhope et al., 2020) formats in chronic pain populations including FM.

Beyond pandemics, teletherapy approaches such as online FIBROWALK (Serrat et al., 2021a) are highly promising when compared to traditional face-to-face when dealing with specific logistic barriers such as time, travel or access difficulties in rural areas, or health barriers such as patients’ fatigue, among other symptoms which may interfere with treatment adherence. Online programs which are highly scalable and accessible per definition may also help in decongest healthcare services (which are particularly overstretched worldwide since the COVID-19 pandemic), significantly reduce healthcare staff costs, and help increase widespread access to evidence-based treatment for FM (Assefi et al., 2003; Friedman et al., 2012; Moman et al., 2019). In this regard, in a recent systematic review on the efficacy of online psychological interventions for people with chronic health conditions, online treatments were found to be efficacious for improving depressive symptomatology and distress in people with FM, supporting the usefulness of these low cost, easily accessible, and highly scalable therapeutic approaches for treating this syndrome (White et al., 2020). Furthermore, an important aspect when implementing treatments, especially for chronic conditions, is to promote self-management and online interventions may facilitate this aspect (Leadley et al., 2012). Simultaneously, nature-based therapeutic approaches such as the outdoor FIBROWALK (Serrat et al., 2020) have shown to be useful in improving mental health in different clinical conditions (Trøstrup et al., 2019), including chronic pain and FM (López-Pousa et al., 2015; Serrat et al., 2020; Stanhope et al., 2020). In this sense, it is interesting that therapeutic programs conducted outdoors have been shown to be effective in improving mental health, pain and general health, and it is suggested that exposure to the natural environment (both in urban green areas and in nature) may produce additive positive effects at both affective (positive and negative emotions and stress) and cognitive (attention, memory, motivation, *etc.*) levels thus enhancing the beneficial effects of the program (Buckley et al., 2018). In this regard, when compared to therapeutic exercise conducted indoors, exercising in natural settings was associated with greater feelings of revitalization and positive engagement, reductions in tension, confusion, anger, and depressive symptomatology, and increased energy (Thompson Coon et al., 2011). Furthermore, there is evidence that exercising outdoors (vs. indoors) may also promote directed attention and social interactions, which may positively influence future intention of maintaining an exercise routine (Rogerson et al., 2016). Regarding the possible effects of the intervention format of the FIBROWALK intervention was found to be beneficial in hospital, outdoors and virtual settings at short term with apparently larger effect sizes in the outdoor format when compared to indoor hospital or online settings (Serrat et al., 2020; Serrat et al., 2021a; Serrat et al., 2021b; Serrat et al., 2022b). However, no clinical trial with a parallel design has yet been conducted to evaluate potential differences in the short- and the long-term efficacy between these different formats or in therapeutic adherence. The present study aims to address this important knowledge gap.

Although recommended, there is a striking lack of empirical evidence regarding the cost-effectiveness of multicomponent interventions for FM, including FIBROWALK. Bearing in mind that costs are of crucial relevance for policy-makers, who usually consider as first-choice treatment those therapeutic approaches with the lowest associated cost per quality-adjusted life-year (QALY), economic evaluations of multicomponent interventions in FM should be performed to ensure (if cost-effective) their implementation in healthcare systems.

### 1.2 Immune-inflammatory status and BDNF levels in individuals with FM

There are several potential physiological factors which have been proposed underpinning the FM symptomatology. In this regard, the central nervous system (CNS) seems to have a leading role (Häuser et al., 2015), involving altered function in pain neural pathways (Sluka and Clauw, 2016; Sawaddiruk et al., 2017). At the same time, there is evidence suggesting an imbalance between pro- and anti-inflammatory cytokine levels at both the peripheral and central levels in individuals with FM contributing to a chronic state of low-grade inflammation (Rodriguez-Pintó et al., 2014; Bäckryd et al., 2017; Albrecht et al., 2019; Andrés-Rodríguez et al., 2019). This proinflammatory state may be a key contributor to impaired pain processing as could lead to the sensitization of peripheral nerves and to central sensitization (Rodriguez-Pintó et al., 2014; Littlejohn, 2015), possibly through activation of glial cells (Nijs et al., 2017).

A recent meta-analysis concluded that patients with FM may present increased levels of blood IL-6, IL-4 and IL-17A compared to healthy controls (Andrés-Rodríguez et al., 2020). Coherently, increased levels in other markers indicative of an inflammatory state [e.g., high-sensitivity C-reactive protein (hs-CRP)] were also reported (Andrés-Rodríguez et al., 2020). Some of these proinflammatory cytokines (e.g., IL-6) are known to facilitate sensitization of peripheral nerves to nociceptive stimuli and to increase the activity of the hypothalamic-pituitary-adrenal axis, as well as prostaglandin and substance P synthesis, thereby reducing the pain threshold (Zhou et al., 2016). On the other hand, at a central level, pro-inflammatory cytokines along with other inflammatory-related by-products are known to alter the synthesis, reuptake and release of different neurotransmitters in the CNS (e.g., serotonin, noradrenaline, dopamine, glutamate. These neurotransmitters are involved in both pain perception and the regulation of diverse affective, cognitive and motivational processes, contributing to the neuroplastic changes observed in FM, abnormal pain experience and to other FM symptoms, such as fatigue, sleep disturbances, cognitive impairment, and affective problems (Miller et al., 2013; Rodriguez-Pintó et al., 2014; Andrés-Rodríguez et al., 2020).

Several studies have suggested that FM and other central sensitivity syndromes present not only with chronic low-grade inflammation but also with abnormalities in biomarkers related to neuronal plasticity, such as BDNF (Deitos et al., 2015). The BDNF is a multifunctional neurotrophin with numerous functions in the brain (Jensen et al., 2012; Cagnie et al., 2014), including a driving force behind (maladaptive) neuroplasticity and central sensitization (Nijs et al., 2015), and it is believed to be specifically associated with the occurrence and/or progression of mnemonic symptoms associated with a variety of conditions characterized by cognitive impairment (Napadow et al., 2012). BDNF is known to play a key role in a variety of neuroplasticity processes, including pain modulation, pain transduction, nociception, and hyperalgesia (Nugraha et al., 2012), all of which are known to be altered in FM. In this regard, plasma levels of BDNF have also been found to be augmented in individuals with FM (Haas et al., 2010; Polli et al., 2020) and DNA methylation in exon nine appears to be driving the higher BDNF protein levels in patients with FM (Polli et al., 2020); however, we have to bear in mind that associations between BDNF levels and patients’ clinical complaints have not been found always consistent (Zanette et al., 2014; Jha and Trivedi, 2018) and that some studies have found no differences between FM patients and healthy controls on BDNF levels (Ranzolin et al., 2016). Furthermore, there are reciprocal associations between BDNF and immune-inflammatory pathways, which may explain the involvement of BDNF in the immune pathophysiology of mood disorders (Perrot and Russell, 2014), with BDNF acting as a conserved regulatory process that protects against the detrimental effects of immune activation including neurotoxicity (Mehterov et al., 2022).

Some of these biomarkers may also influence treatment response in individuals with chronic pain conditions including FM. Related to this, higher pretreatment levels of IL-6 and TNF-α have been found to be associated with lesser improvements in pain intensity and other patient-reported outcomes after cognitive behavioral interventions administered in individuals with chronic pain (Lasselin et al., 2016). Furthermore, higher baseline levels of CXCL8 were also found to attenuate clinical benefits (i.e., in pain, fatigue, stiffness and quality of sleep) after an 8-week standardized mindfulness program in patients with FM (Andrés-Rodríguez et al., 2019).

### 1.3 Effects of non-pharmacological interventions on immune-inflammatory markers and BDNF in individuals with FM

In a systematic review of longitudinal studies in FM, multicomponent programs, physical exercise and dietary modification were found to have effects on inflammatory markers in FM patients (Sanada et al., 2015). In this regard, reductions in levels of the pro-inflammatory cytokines IL-6 and CXCL8 were observed in FM patients following these interventions, suggesting a potential anti-inflammatory effect. Similarly, in a recent study (Andrés-Rodríguez et al., 2019) evaluating the effects of mindfulness training on immune-inflammatory markers, it was also reported that levels of the anti-inflammatory cytokine IL-10 remained higher in patients assigned to mindfulness than those allocated to the TAU arm. In another study assessing the effects of an 8-week compassion-based intervention (i.e., Attachment-Based Compassion Therapy, ABCT) for FM, a global anti-inflammatory effect along with reductions in BDNF levels in individuals with FM when compared to an active control condition (i.e., relaxation training) were also reported (Montero-Marin et al., 2019). These changes in BDNF levels were significantly related and followed by ameliorations in FM functional impairment, showing significant indirect effects, which means that reductions in BDNF might function as a crucial treatment mediator. In this study, baseline BDNF levels were similar to those obtained in a previous study with patients suffering from central sensitivity syndromes with persistent somatic or visceral nociception in which, after treatment, these levels normalized, approaching to those observed in pain-free individuals (Deitos et al., 2015). Regarding the effects of psychosocial interventions (mainly psychotherapy and psychoeducation) on immune function in adults with different health conditions, in an extensive systematic review and meta-analysis (Shields et al., 2020), many different improvements in immune function (including levels of pro-inflammatory biomarkers) were robustly reported. Interestingly, these effects were more remarkable after the application of CBT and multicomponent programs. Importantly, there are no available studies assessing the effects of multicomponent interventions such as FIBROWALK in physiological markers in fibromyalgia aimed at understanding physiological mechanisms underpinning its efficacy.

The objectives of the On&Out study are 1) to examine the effectiveness and cost-utility of adding the FIBROWALK intervention in online or in outdoors format to TAU in the management of patients with FM for improving functional impairment (primary outcome) and pain, fatigue, depressive and anxiety symptoms, perceived stress, central sensitization, physical function, sleep quality and perceived cognitive dysfunction (secondary outcomes); 2) to identify pre–post differences in levels of different physiological variables (i.e., immune-inflammatory markers and BDNF levels) and correlate these changes with those observed at self-report measures and 3) evaluate the role of psychological process variables considered to be potential mediators of the interventions from a theoretical point of view (i.e., kinesiophobia, pain catastrophizing, psychological inflexibility in pain and pain knowledge) and the evaluated physiological variables as mediators of long-term clinical improvements. For the sake of personalized treatment in FM, the design of the present study will allow us to explore whether certain patient profiles or baseline psychobiological characteristics may help predict the short- and long-term clinical response to the specific evaluated treatments.

## 2 Materials and methods

### 2.1 Trial design

This RCT protocol was developed following the Standard Protocol Items: Recommendations for Interventional Trials (SPIRIT) (Chan et al., 2013) and was recorded in the ClinicalTrials.gov trial register in May 2022 (NCT05377567). We designed a 6-month, parallel group, randomized (using a computer-generated randomization list), single-blind, controlled trial (RCT) with three treatment arms. The effectiveness of the FIBROWALK program (i.e., multicomponent program based on therapeutic exercise, PNE, CBT, and mindfulness training) in FIBRO-On (online) and in FIBRO-Out (outdoors) formats adjuvant to TAU, compared to TAU alone in patients with FM recruited from the Central Sensitivity Syndromes Specialized Unit from the HUVH, will be evaluated. The Consolidated Standards of Reporting Trials 2010 (CONSORT) (Schulz et al., 2010) and the Consolidated Health Economic Evaluation Reporting Standards (CHEERS) (Husereau et al., 2013) will be followed. The expected flowchart of participants in the study is displayed in Figure 1.

**FIGURE 1 F1:**
[figure not shown]
Flowchart of the On&Out study based on the Consolidated Standards of Reporting Trials guidelines. Fibro-Out, FIBROWALK Outdoors; Fibro-On, FIBROWALK Online; ITT, intention-to-treat; TAU, Treatment-As-Usual.

### 2.2 Recruitment strategy

Potential participants are individuals with FM diagnosis (ACR 2010/2011 criteria) made by a rheumatologist and seeking health services currently or in the last year at the Central Sensitivity Syndromes Specialized Unit at HUVH.

### 2.3 Sample size calculation

Two-hundred and twenty-five individuals who meet the selection criteria for the study will be recruited. The estimated sample size needed is n = 63 participants per condition considering a moderate effect size (Cohen’s d = 0.5) for the difference between the active arms at post-intervention compared to the control group for the primary variable (i.e., FIQR score) with an alpha = 0.05 and 1-b power = 0.80. With an expected dropout rate of 20%–25%, the final sample size is estimated at 75 individuals per arm. The effect size used for the sample size calculation corresponds to the average effect size for multicomponent interventions in FM vs. control group (Nüesch et al., 2013). Previous RCTs evaluating the FIBROWALK intervention indicated effect sizes between d = 0.4 (Serrat et al., 2021a) and d = 1.83 (Serrat et al., 2020). Using as a reference previous studies of the group evaluating the effect of different non-pharmacological treatments in FM patients on blood values of immuno-inflammatory markers (Andrés-Rodríguez et al., 2019; Montero-Marin et al., 2020), it is estimated that a sample size of 40 subjects per arm will be sufficient to be able to detect changes in the evaluated variables.

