### 2.5 Procedure and randomization

The recruitment of participants will be carried out in two ways: 1) consecutive recruitment from consultation by the rheumatologists of the HUVH Central Sensitivity Syndromes Specialized Unit and 2) by screening a list of patients (with contact telephone number) corresponding to patients who contacted the Unit during the last 6 months. The clinicians involved in the project (i.e., MA and MS) will proceed to carry out the telephone screening and those who meet the selection criteria of the study will be invited to participate. After obtaining written informed consent, the instrument battery -including clinical and economic measures-described below will be administered (online assessment). Two research assistants will coordinate the study assessments to ensure an adequate understanding of all administered self-reported measures. Random assignment of participants to study arms will be executed after baseline assessments as recommended by the CONSORT guidelines (Schulz et al., 2010). Once written consent and baseline assessment have been completed, study participants will be given a unique personal code and randomized using randomization software (1:1:1 ratio). The computer-generated randomization will apply a permuted block design to ensure that the groups are balanced taking biomarkers substudy eligibility criteria (No=Not meeting criteria for biomarkers substudy; Yes = Meeting criteria) into account. The randomization list will be stored in an encrypted file on a password-protected computer in the clinical trials supervisor’s office to assure concealment of allocation. Participants will be informed of their group allocation by the administrative personnel, who will send a notification *via* email.

Patients who meet the selection criteria for the biomarkers substudy will be rescheduled 3–5 days after the first assessment to obtain blood samples (up to the required N of 40 subjects per arm). Fasting blood extractions will be performed in a pre-set time window (8a.m.–10a.m.) to reduce circadian variability in the levels of the biomarkers evaluated. In order to limit the effects of medication on the study variables, patients will be asked to refrain from taking any occasional anti-inflammatory drugs in the 72 h prior to blood sampling.

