The research assistants, who will be blinded to randomization, will coordinate the three subsequent clinical assessments: at 6 weeks, at post-intervention and at 6 months after the baseline assessment (follow-up). The same procedure as in baseline will be followed for the collection of biological samples at post-intervention, respecting the pre-set time interval.

The study will be organized in two consecutive periods with six study groups (i.e., 2 TAU, 2 FIBRO-Out, 2 FIBRO-On) conducted in parallel in each period. All the groups will include 18–20 participants (i.e., FIBRO-On, FIBRO-Out, TAU), so the N = 75 is expected to be reached at the end of the study.

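### Section 2.3: 75 randomised per arm does not leave the required 63 after 20%–25% dropout, so the stated calculation does not support 80% power

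*Protocol article*

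**What the plan says.** The sample size is set in Section 2.3 of the protocol article. The target is "The estimated sample size needed is n = 63 participants per condition", derived "considering a moderate effect size (Cohen’s d = 0.5) for the difference between the active arms at post-intervention compared to the control group" on the FIQR, "with an alpha = 0.05 and 1-b power = 0.80". The next step allows for attrition: "With an expected dropout rate of 20%–25%, the final sample size is estimated at 75 individuals per arm". The total agrees with that figure: "Two-hundred and twenty-five individuals who meet the selection criteria for the study will be recruited", that is 3 × 75, allocated 1:1:1 (Section 2.5).

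Section 2.5 describes two periods with two groups per arm in each. That is four groups of 18–20 per arm, or 72–80 people, "so the N = 75 is expected to be reached at the end of the study".

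Section 2.11.1 analyses the FIQR by intention to treat, with a REML mixed model on the repeated assessments and without imputation. Section 2.3 does not refer to that model.

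**The concern.** The inflation step is meant to ensure that the required number is still available after the expected losses. Here the required number, the dropout range and the final size are all printed, and they cannot all be right. No dropout rate between 20% and 25% takes 75 down to 63.

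What is at stake is the power statement. It will be carried into the results paper, and any non-significant FIQR contrast will be read against it. If the plan's own dropout assumption proves correct, the type II error on the plan's own calculation is about 22%–25%, not 20%.

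**Working it through.** **Inputs (Section 2.3):** d = 0.5; alpha = 0.05; power = 0.80; 63 needed per arm; dropout 20%–25%; 75 per arm randomised. Sidedness is not stated. Two-sided is assumed because it reproduces the 63; a one-sided test would need only 50.

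**Step 1: reproduce the 63.** Normal approximation for two means: n = 2 × (1.960 + 0.842)² / 0.5² = 62.8, so 63 per arm. The plan's figure reproduces. The t-test version gives 63.8, so 64.

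**Step 2: inflate for dropout.** The number randomised is 63/(1 − dropout).
- 20%: 63/0.80 = 78.75, so 79 per arm (237 in total).
- 25%: 63/0.75 = 84 per arm (252 in total).

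The stated 75 matches neither end. The dropout that 75 can absorb is 1 − 63/75 = 16%.

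**Step 3: what 75 leaves.**
- 20%: 75 × 0.80 = 60, which is 3 short of 63.
- 25%: 75 × 0.75 = 56.25, so about 56, which is 7 short.

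**Step 4: power at d = 0.5.** Normal approximation: power = Φ(0.5 × √(n/2) − 1.960).

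| Evaluable per arm | Normal approximation | t-test |
|---|---|---|
| 63 (plan's target) | 0.801 | 0.795 |
| 60 (20% dropout) | 0.782 | 0.775 |
| 56 (25% dropout) | 0.754 | 0.746 |

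On either method, dropout costs about 2 points at 20% and about 5 points at 25%. The t-test column starts about half a point lower, so part of any gap between it and 0.80 comes from the method, not from dropout. The effect detectable with 80% power on the t-test moves to about d = 0.52–0.53.

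**Step 5: can the planned group sizes absorb the loss?** Four groups filled to 20 give 80 per arm. That leaves 80 × 0.80 = 64 at 20% dropout, but only 80 × 0.75 = 60 at 25%. The 84 needed at 25% exceeds the stated group capacity.

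**The case against.** **The primary model uses more data than the calculation assumes.** This is the strongest objection. The FIQR is measured at baseline, 6 weeks, 12 weeks and 6 months, and under the mixed model a participant lost after 6 weeks still contributes. With all 75 per arm and no loss, power would be 0.86–0.87, so true power depends on how much information the dropouts supply. Baseline adjustment could also help. If the baseline–outcome correlation were 0.5 (an assumption; the documents give none), t-test power scaled by d/√(1 − r²) would be about 0.86 with 56 per arm and 0.88 with 60. At a correlation of 0.3 it would be about 0.79 and 0.81. This stands as a reason not to call the trial underpowered. It does not rescue Section 2.3, which sizes a simple two-group contrast, treats dropouts as lost and states no correlation.

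**The dropout range may refer to 6 months.** The effect size is set at post-intervention (12 weeks), whereas the 20%–25% is tied to no time point. The Discussion expects more dropout than in earlier short-term studies and cites adherence above 90% in those. If the range is loss to 6 months, loss at 12 weeks could be 16% or less, which 75 would cover. This reading is possible, but the document does not state it or give a 12-week rate.

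**The 75 might mean completers.** Section 2.5 speaks of reaching 75 at the end of the study. However, 225 are to be recruited and allocated 1:1:1, and the groups hold 72–80 per arm, so 75 is the number randomised.

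**The loss is small.** This is correct, and it limits the weight of the point. It does not make the printed figures agree.

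**Conclusion.** Section 2.3 is internally inconsistent. Its own inputs require 79–84 randomised per arm, not 75. With 75, 56–60 remain and power at d = 0.5 is about 0.75–0.78 on the plan's own two-group calculation. This assumes a two-sided test and that dropouts contribute nothing to the 12-week contrast, which is how the section treats them.

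A reader might go further in three ways that the document does not support:
- **That the trial fails to reach 80% power.** This is not shown, because the mixed model may recover the shortfall. What is shown is that the stated calculation does not support the claim.
- **That power for FIBRO-On is far lower because of this error.** Section 2.3 says earlier FIBROWALK trials "indicated effect sizes between d = 0.4" upward, and the lower figure comes from a trial of the online format. But neither the outcome nor the time point behind it is given, the article cites a second online trial whose effect is not given separately, and 0.5 has its own stated source. Low power at d = 0.4 is also not caused by dropout: with all 63 evaluable it is only Φ(0.4 × √31.5 − 1.960) = 0.61.
- **That the authors multiplied by 1.2 instead of dividing by 0.8.** 63 × 1.2 = 75.6 is close to 75, but this is an inference about origin, and the inconsistency does not depend on it.

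**What to change.** Amend Section 2.3 in one of these ways:
1. Keep 75 per arm, and state that 20%–25% dropout leaves 56–60 evaluable, with power of about 0.75–0.78 at d = 0.5 and a detectable d of about 0.52–0.53.
2. State and support a dropout of at most 16% at 12 weeks, and give the 20%–25% separately if it refers to 6 months.
3. Justify 80% power under the planned mixed model, with the assumed correlation and its source.

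Filling the planned groups to 20 would help at 20% dropout (64 left) but not at 25% (60 left), so it is not a full remedy. Power at d = 0.4 may be added as an optional sensitivity figure (t-test about 0.58 with 60 per arm and 0.56 with 56), kept apart from the dropout correction.

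Options 1 to 3 need only a few sentences and no change to design or recruitment. Option 1 makes the stated power slightly less favourable.
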